### Analysis

We shall analyse all data by intention to treat. We shall use Cox regression, a form of survival analysis that takes account of covariates, to analyse relapse and recurrence. We shall analyse most other measured variables by mixed-model analysis of variance (ANOVA). We shall use baseline values of the dependent variable as a covariate in all analyses; we shall use other baseline measures or demographic characteristics as covariates when they contribute significantly to the analysis. We shall use multi-level modeling to take account of the clustering of participants within classes within centres. To minimise testing, we shall combine measured outcomes at different time points using the 'area under (the resulting) curve'. We shall use cognitive measures to explore the extent to which they mediate relapse and recurrence during treatment and follow up. Similarly we shall use data at each time-point on the Beck Scale for Suicide Ideation to explore the extent to which the cognitive measures mediate the occurrence of suicidality over the follow-up period, again analysing 'area under the curve'. Additionally we shall examine recurrence of suicidality specifically for those participants who relapse to Major Depression (MDD) and had a history of suicidal ideation or behaviour at entry to the trial. We predict that, all else being equal, suicidal ideation will fall in those who have received treatment with MBCT. Further details of the data analysis plans are given in Appendix 1.

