We encourage all participants to continue their 'treatment as usual' as determined through consultations with their GP and other mental health professionals, for the duration of the study. In addition we ask those not allocated to MBCT not to take up a regular meditation practice over the year of follow-up, and thus to restrict their choice of treatment. As we cannot enforce this in practice, we ask at each assessment whether participants have taken up any treatment or meditation practices so that we can take this into account in analysis. Furthermore we shall offer all participants, especially those receiving TAU alone, treatment classes of their choice after the end of the study. The research team will maintain contact with those in the TAU group throughout the trial, and encourage them to make full use of the services available to them. As participants may relapse to suicidal depression during the study, we explain the limits of confidentiality and the procedure for dealing with severe suicidal ideation to all participants before asking them to give consent.

In summary, recurrent depression is common and gives rise to increased risk of morbidity and mortality for those who become suicidal when depressed. There is an urgent need: first to develop treatments that can address the needs of this group and produce sustainable reductions in risk of recurrence; and, second to identify the critical therapeutic factors in order to refine the approach for the future. This trial will address both objectives.

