## Appendix 1: Statistical Analysis Plan

The primary outcome measure will be the time to relapse or recurrence meeting DSM-IV criteria for a major depressive episode (American Psychiatric Association, 1994) on the Structured Clinical Interview for DSM-IV (SCID, Spitzer et al., 1992). Occurrence of relapse or recurrence will be assessed after treatment (T1), and at three (T2), six (T3), nine (T4) and twelve (T5) months thereafter by trained psychologists blind to participants' treatment condition. If the interview establishes that symptoms meeting diagnostic criteria for major depression have been present since the last assessment, we shall ask participants when this episode of depression started (and ended, if they are no longer symptomatic). 'Return to treatment' will also be treated as a relapse or recurrence if, in the judgment of a blind rater, the participant experienced exacerbation of their symptoms that would have met the criteria for Major Depression in the absence of immediate treatment.

The analysis will be by 'intention to treat' (ITT). The time (in weeks) of relapse or recurrence to Major Depression, as defined above, will be the dependent variable in survival analysis. The treatment group and stratification variables will be used as predictors.

For participants who are lost from the trial we shall use their available measures and then censor them at the time of their last observation. Since only a participant's first relapse or recurrence to Major Depression will contribute to the survival analysis, the subsequent loss of that participant will not affect the analysis.

Participants who miss one or more follow-up assessments, but are then assessed at a later time point will be asked whether they have experienced a relapse or recurrence according to SCID diagnostic criteria since the last assessment, including time periods which would have been covered in missed assessments. This will enable us to assess the time to relapse and thus to censoring.

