We shall use the clinician-rated Hamilton Rating Scale for Depression (HRSD, to assess severity of depression at all time points. We shall follow De Rubeis et al. (2005) and Hollon et al (2005) in using a score of 14 or more on the HRSD to indicate relapse, thus complementing the SCID diagnosis. HRSD scores also provide a quantitative measure of outcome that strengthens the dichotomised outcome of diagnosis, because, as a quasi-continuous measure, it has more power to detect differences between groups.

The other quantitative measures used at baseline, before treatment, and at times T1 to T5 are the Beck Depression Inventory (BDI-II), Beck Hopelessness Scale (BHS), Beck Scale for Suicide Ideation (BSS current) and the EQ5D. We shall calculate the 'area under the curve' (AUC) of each measure to give a single score. For the EQ5D this is known as a QALY.

Missing items within individual outcome measures will be treated according to the instructions for that measure. If two or more observations for quantitative measures are available between T1 and T5, then we shall use linear regression to estimate the missing values and the AUC. If there is only one observation available between T1 and T5 then we shall estimate the remaining values from the general slope estimated from all participants with two or more observations. If no observations for T1 to T5 are available then the AUC is also missing. If the trend among participants with full data departs from linear, then we shall use the observed trend to estimate the missing values.

For the quantitative measures we shall use a mixed-model analysis of covariance (AnCova). We shall use baseline measures as covariates, and multi-level modeling to take account of the clustering of participants within classes within centres. As covariates we shall also use the stratification variables and treatment group, together with the number of sessions attended and, in the MBCT group, number of hours of home practice. These will allow us to estimate how the response to the two treatments depends on their 'dose'.

Potential moderators to be examined include gender, residual symptoms of depression (e.g. HRSD score and BDI-II score at baseline) and stability of remission, course of previous history (chronic vs episodic), and age of onset.

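### The only AnCova stated for the main quantitative outcomes adjusts treatment group for sessions attended and MBCT home practice, so its treatment coefficient need not be the declared intention-to-treat effect

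*Protocol article*

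**What the plan says.** Appendix 1 (Statistical Analysis Plan) names the method for the quantitative outcomes: "For the quantitative measures we shall use a mixed-model analysis of covariance (AnCova"). It takes baseline measures as covariates and models the clustering of participants in classes and centres. It then adds treatment group and the stratification variables, and in the same sentence "treatment group, together with the number of sessions attended and, in the MBCT group, number of hours of home practice". The next sentence gives the reason: "These will allow us to estimate how the response to the two treatments depends on their 'dose". Appendix 1 sets out no AnCova for these measures without the dose terms.

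Two other places differ:

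- The Analysis section states "We shall analyse all data by intention to treat". Beyond the baseline value of the outcome, the covariates it names are of one kind: "we shall use other baseline measures or demographic characteristics as covariates when they contribute significantly to the analysis".
- For the primary time-to-relapse model, Appendix 1 has no dose terms: "The treatment group and stratification variables will be used as predictors".

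**The concern.** Both dose variables are observed after randomisation and are part of what was allocated. TAU has no classes, so its sessions are zero by construction. Home practice is entered for MBCT alone, so it is zero or undefined elsewhere. A model holding treatment group and these variables together splits the effect of allocation into a part credited to dose and a remainder credited to group. The remainder is not the intention-to-treat effect.

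The MBCT versus CPE contrast is the most exposed. According to Trial Objectives and Purpose, CPE is MBCT without meditation, so that the contrast isolates what meditation adds. Practice hours largely measure meditation done at home, and adjusting for them can remove the effect that the contrast is there to show. Adherence may also share causes with outcome, which would bias the dose slopes and, through them, the group coefficient.

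At stake are the between-arm estimates on HRSD, BDI-II, BHS, BSS and EQ5D. Appendix 1 relies on the HRSD in particular to strengthen the yes/no diagnosis, because a near-continuous score has more power.

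**Working it through.** **1. The plan's own figure (Sample Size).** Inputs: 120 MBCT, 120 CPE, 10 per class, ICC 0.05, 80% power, 5% level (taken as two-sided).

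- Design effect: 1 + (10 - 1) × 0.05 = 1.45.
- SE of the difference in SD units: √(2 × 1.45/120) = 0.155.
- Detectable difference: (1.96 + 0.84) × 0.155 = 0.44 SD. With t quantiles on 22 df (24 classes) it is 0.456 SD.

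These bracket the stated 0.45 SD. That figure belongs to a model without dose terms.

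**2. What the coefficient estimates when the dose terms enter.** Let S be sessions and H practice hours, uncentred, with S = 0 in TAU and H = 0 in CPE and TAU. Let g_S and g_H be their fitted slopes. Leaving the baseline covariates aside, least squares gives:

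- MBCT minus CPE coefficient = ITT effect - g_S × (mean S in MBCT - mean S in CPE) - g_H × mean H in MBCT.
- MBCT minus TAU coefficient = ITT effect - g_S × mean S in MBCT - g_H × mean H in MBCT.

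The coefficient equals the ITT effect only if the subtracted terms cancel or are zero.

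**3. Size of the shift.** Assumptions, not in the documents: about 6 of 8 sessions, 30 practice hours on average (SD 10), and a true MBCT minus CPE effect of -0.45 SD. The mean hours cancel when the benefit runs through hours. If a fraction f of the benefit does so, g_H × mean H = -0.45f and the coefficient is -0.45 × (1 - f): -0.45 at f = 0, -0.225 at f = 0.5, and 0 at f = 1.

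Simulation (2,000 trials per scenario, 120/120/60, ICC 0.05, least squares without the random class term, mean model-based SE) agrees. Without dose terms MBCT minus CPE is -0.45 (SE 0.13 to 0.14) throughout, to within 0.01. With them:

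| Scenario | MBCT - CPE (SE) | MBCT - TAU (SE) |
|---|---|---|
| Constant effect, dose irrelevant and unconfounded | -0.45 (0.31) | -0.45 (0.39) |
| Benefit wholly through hours | 0.00 (0.31) | 0.00 (0.39) |
| Sessions help both class arms, hours help MBCT (ITT effect v TAU -0.65) | 0.00 (0.31) | -0.02 (0.39) |
| Hours slope steeper than the mean effect (-0.65 at 30 hours, offset +0.20) | +0.19 (0.31) | +0.19 (0.39) |
| No dose effect, but a prognostic factor lowers adherence | +0.07 (0.34) | +1.20 (0.43) |

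The last row depends heavily on the assumed strength of confounding. Other choices gave MBCT minus CPE between -0.06 and +0.39.

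**4. Loss of precision where there is no bias.** The hours slope is estimated from 120 MBCT participants, so its contribution to the variance of MBCT minus CPE is about (mean H/SD of H)²/120. With r for that ratio, SE ≈ √((2 × 1.45 + r²)/120) and the detectable difference is 2.80 × SE:

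- r = 1: √(3.9/120) = 0.18, detectable 0.50 SD.
- r = 2: √(6.9/120) = 0.24, detectable 0.67 SD.
- r = 3 (30 hours, SD 10): √(11.9/120) = 0.315, detectable 0.88 SD.

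The simulated SE of 0.31 gives 2.80 × 0.31 = 0.87 SD. A run that carried the class clustering into the SE moved it from 0.16 to 0.33, which gives 2.80 × 0.33 = 0.92 SD. The result depends on r, not on the number of hours itself.

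**The case against.** The strongest defence is purpose. Appendix 1 says that the dose terms serve a dose-response question, and the Analysis section describes the same family of models with baseline covariates under intention to treat. Together these could mean an intention-to-treat comparison plus a dose extension, run together in a condensed appendix. That may be what was intended. But the appendix lists treatment group and the dose terms in one sentence for one model, and names no other from which the between-arm effect would come.

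A second defence is coding. If dose is centred within arm, the contrast returns to -0.45 SD with no loss of precision, whether the effect is constant, runs through hours, or adherence is confounded. This is right, and it makes the hazard conditional. The appendix states no centring, and ordinary entry gives the results shown above.

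Three stronger readings are tempting and not supported:

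- A reader might infer that every secondary comparison will be biased. With a constant effect and unconfounded adherence, only precision is lost. The AnCova for suicidal cognitions at T1 and T5 names only T0 as covariate, so it is outside this point.
- A reader might infer that the trial's main test of meditation is adjusted away. Time to relapse is modelled on treatment group and stratification variables only.
- A reader might take the Discussion, where participants are asked whether they "have taken up any treatment or meditation practices so that we can take this into account in analysis", as a commitment to adjust for later uptake. It names no covariate, model or outcome, and would fit a descriptive or sensitivity analysis equally well.

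**Conclusion.** The point stands for the quantitative measures that Appendix 1 assigns to the mixed-model AnCova: HRSD, BDI-II, BHS, BSS and EQ5D. The stated model conflicts with the declared intention-to-treat analysis and with the baseline-only covariates of the Analysis section. Entered uncentred, its treatment coefficient can shrink to nothing or change sign if benefit runs through practice or adherence is related to prognosis. In the unbiased case its standard error roughly doubles at about 6 sessions and 30 hours (SD 10), and the 0.45 SD in Sample Size no longer holds.

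That any dose slope shifts the coefficient follows from the structure of the model. The sizes rest on dose distributions, effect sizes and confounding that the documents do not give, so they are illustrations and not forecasts. Because the primary analysis is untouched, this is a should-fix matter for secondary outcomes.

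**What to change.** In Appendix 1, state that between-arm effects on these measures are estimated from an AnCova with treatment group, the baseline value of the outcome, the stratification variables and the clustering terms, and no variable observed after randomisation. Move sessions attended and home-practice hours to a separate dose-response analysis within the active arms, labelled exploratory, with a note that its slopes are open to confounding by prognosis.

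The cost is about two sentences. No data collection changes, the dose question is still answered, and the 0.45 SD detectable difference again matches the model that is fitted. The change should be made before the arms are compared.

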### The Interventions

The two treatments, MBCT and CPE, both consist of 8 weekly classes of two hours duration. MBCT [4] is a manualised treatment programme that combines training in mindfulness meditation with cognitive therapy techniques which has been adapted for this trial by [name] and colleagues ([name], [name], [name] and [name]) for patients with a history of suicidality. In addition to weekly meetings, we advise participants to spend about an hour per day on home-based practice which includes regular meditation practice and smaller tasks aimed at cultivating mindfulness in everyday life. The rationale of the treatment is based on research suggesting that, in vulnerable individuals, negative thinking patterns can be easily re-activated through only minor events like subtle changes in mood, and that negative mood is often perpetuated through maladaptive habitual patterns of thinking that are characterized by ruminative tendencies and avoidance. Through meditation practice, MBCT aims to help participants to become aware of re-activation of negative thinking at earlier stages and to disengage from maladaptive reactions such as ruminative and avoidant tendencies, which might otherwise ensue. Participants learn to relate to all their experience with openness and acceptance. MBCT has been found to reduce successfully the risk of relapse in patients with three or more episodes of depression in the past. Previous work from our group has shown that cognitive reactivity is particularly pronounced in patients who have suffered from suicidal depression in the past [10], suggesting that MBCT might be particularly helpful as a treatment approach to reduce vulnerability in this group.

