### Pre-Class Interviews

We tell all participants the outcome of randomisation by letter (in addition to email or telephone if requested). We invite those allocated to MBCT or CPE to meet the therapist running their class and those in TAU to meet another member of the research team. These meetings take between 1 and 1.5 hours and either prepare participants for classes, including discussion of ways of coping with barriers to treatment, or discuss procedures for keeping in touch with participants not in classes.

Each week of the eight-week treatment phase, we ask all participants to complete a brief set of tracking questionnaires. These include short ratings of tendencies to ruminate, occurrence of intrusive thoughts, thought suppression, and the PHQ9 and GAD7 scales for assessing symptoms of depression and anxiety. At the start of the second class we also ask participants receiving MBCT or CPE to rate the plausibility of their treatment. Finally participants receiving MBCT complete a short diary documenting homework and practice completed throughout the week.

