### Withdrawal

Participants can withdraw from treatment or data collection or both at any time without having to give a reason. Nevertheless we ask those who withdraw from the trial treatment (MBCT or CPE) to attend all the remaining research appointments or at least to provide minimal data if they are willing.

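### The coefficients of sessions attended and home-practice hours are presented as showing how response depends on dose, but they are self-selected, within-arm associations that worsening during treatment could produce on its own

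*Protocol article*

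**What the plan says.** Appendix 1 (Statistical Analysis Plan) sets the model for the secondary measured outcomes: "For the quantitative measures we shall use a mixed-model analysis of covariance (AnCova"). On adjustment it says: "We shall use baseline measures as covariates, and multi-level modeling to take account of the clustering of participants within classes within centres". Stratification variables and treatment group also enter, "together with the number of sessions attended and, in the MBCT group, number of hours of home practice". The stated purpose follows at once: "These will allow us to estimate how the response to the two treatments depends on their 'dose". No caveat is attached.

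Other sections show how dose arises:

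- The Interventions: the two programmes "both consist of 8 weekly classes of two hours duration", so the maximum is eight sessions. For MBCT, "we advise participants to spend about an hour per day on home-based practice"; practice is advised, not assigned.
- Withdrawal: "Participants can withdraw from treatment or data collection or both at any time without having to give a reason". Those who stop treatment are still asked to attend the remaining assessments.
- Pre-Class Interviews: "Each week of the eight-week treatment phase, we ask all participants to complete a brief set of tracking questionnaires". These include the PHQ9 and GAD7. The dose model does not mention them.

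**The concern.** A regression coefficient shows how response depends on dose only if, given the other terms in the model, the dose a person received is unrelated to how that person would have fared anyway. Here dose is chosen during the eight weeks, while mood can already be changing; the T1 interview is designed to record changes in diagnostic status over that period. Someone who worsens in week 3 may miss later classes, practise less and score worse from T1 onwards. Because leavers are still followed up, such people stay in the analysis.

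What is at stake is a reported finding, on the secondary outcomes, that more sessions or more meditation practice gives a better result, when the data may show only that people who feel worse attend and practise less.

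**Working it through.** **1. What the sessions coefficient measures.** Sessions are zero for everyone in TAU, and arm is in the model. The coefficient is therefore identified only from differences in attendance among participants within MBCT and within CPE. Practice hours vary only within MBCT. Neither comparison is randomised.

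**2. What is adjusted for.** Appendix 1 lists baseline measures, stratification variables and arm. The Analysis section adds other baseline or demographic variables that contribute significantly. All of these precede treatment, so none captures worsening between T0 and T1.

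**3. Size under assumption.** The plan states no figure to reproduce, and the documents give no correlation between attendance and prognosis, so a range is assumed. Inputs from Sample Size: 120 MBCT, 120 CPE, 60 TAU and a 5% level (two-sided assumed). Two simulations set the true dose effect to zero and fitted ordinary least squares on arm, baseline and sessions (0 to 8, mean about 6).

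- Model A (1,500 runs per setting): attendance has correlation r with unmeasured prognosis.
- Model B (3,000 runs per setting): outcome = 0.5 × baseline + 0.5 × W + arm effect + noise of variance 0.5, where W is worsening during treatment. Attendance has correlation −rho with W.

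| Assumed correlation | Model A, sessions | Model B, sessions | Model B, practice hours (MBCT only) |
|---|---|---|---|
| 0 | 5% | 5% | 5% |
| 0.1 | 32% | 13% | 11% |
| 0.2 | 84% | 39% | 23% |
| 0.3 | >99% | 74% | 47% |

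Entries are the share of runs with a dose coefficient significant at 5%.

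**4. Why the models differ.** In Model A, r is in effect the correlation with the whole outcome residual. In Model B the residual variance is 0.25 + 0.5 = 0.75, so W correlates 0.5/√0.75 = 0.577 with it, and the effective correlation is 0.577 × rho.

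A Fisher-z approximation with 240 treated participants confirms this. The expected z is √237 × atanh(r), and the rejection rate is about Φ(z − 1.96).

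- Model A, r = 0.1: z = 1.54, about 34%. r = 0.2: z = 3.12, about 88%.
- Model B, rho = 0.2: effective r = 0.115, z = 1.79, about 43%. rho = 0.3: effective r = 0.173, z = 2.69, about 77%.

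The simulated rates lie slightly lower, as expected when attendance is rounded and capped at 8.

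**5. Size of the false gradient.** In Model B the mean coefficient per session is −0.0545 at rho = 0.2 and −0.0819 at rho = 0.3. Over eight sessions this is 8 × 0.0545 = 0.44 SD and 8 × 0.0819 = 0.66 SD. For scale, Sample Size gives 0.45 SD as the detectable MBCT v CPE difference.

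**6. Limits.** Neither simulation includes clustering, stratification variables or further baseline covariates. The practice-hours model was fitted in MBCT alone, without sessions.

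**The case against.** **The text claims less than a causal effect.** It puts dose in quotation marks and names no hypothesis test. That is fair, and rejection rates are only one way to show the problem. But the sentence still says response depends on dose and gives no caveat, and the bias in the coefficient is there whether or not it is tested.

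**Further baseline covariates could absorb part of the prognosis.** They could. They cannot absorb worsening that begins after baseline.

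**The percentages follow from the assumed correlation.** This stands. The two models disagree by more than a factor of two at 0.1 and at 0.2, and the documents do not show that worsening is frequent enough to reduce attendance much. A reader might take the table as this trial's false-positive rate; nothing in the documents supports that.

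**The key question does not rest on the dose terms.** This also stands. A reader might infer that the search for the critical component is compromised. Trial Objectives and Purpose and the Discussion answer it by the randomised MBCT v CPE comparison, and the Discussion leaves the role of homework to further research. Nor does the point reach the primary analysis: Appendix 1 lists only treatment group and stratification variables as predictors of time to relapse.

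**An instrumental-variable estimate per session would not rescue the dose claim.** Correct. With one binary instrument for each comparison with TAU, it is essentially the intention-to-treat difference divided by mean attendance, and it shows no dose-response shape. Allocation also brings reunion sessions and, in MBCT, home practice, so it does not act through class attendance alone.

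**Conclusion.** The concern holds in a limited form. The sentence on dose claims something the model cannot deliver: the coefficients describe within-arm associations of outcome with self-selected attendance and practice, and worsening during treatment can generate them when dose has no effect. That conclusion needs no numerical assumption beyond the possibility that attendance and in-treatment course are related.

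The size is unknown. Under assumed correlations of 0.1 to 0.3 the illustrative false-positive rate for sessions runs from about 13% to over 99%, according to correlation and outcome model; at zero correlation it is the nominal 5%.

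The reach is the secondary quantitative outcomes. The plan should be changed, but the primary conclusion is not at risk from this point.

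**What to change.** Replace the sentence on dose with a statement that associations of outcome with sessions attended and practice hours, within arm, are exploratory and not causal.

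Fit them in a model separate from the intention-to-treat AnCova. When relating later attendance or practice to outcome, adjust for the PHQ9 and GAD7 scores of earlier weeks, and state that residual confounding may remain.

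Optionally, add a complier average causal effect (CACE) analysis of receiving the treatment package against TAU, with randomisation as the instrument and the exclusion restriction stated. It should not be presented as a per-session dose-response.

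No new data are needed. The cost is a small amount of extra analysis and a weaker claim about dose.

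Moving the dose terms to their own model also keeps the treatment coefficient free of post-randomisation covariates. That is a separate matter, and the move alone would not remove the confounding of the dose coefficients.
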